### Organization and statistical processing of data

2.9

The data will be tabulated and treated in the program Bioestat 5.0. The descriptive statistics of the data will be performed. For the evaluation of the association of categorical variables, the Chi-square test and Fisher's Exact Test will be used. To compare the means, the Student's *t* test and Analysis of variance (ANOVA) will be used and to analyze the correlation between the continuous variables the test of Pearson correlation will be applied. In the analyzes of the experimental differences in each group the Wilcoxon test will be used. For all analyzes a level of significance of 95% (*P* < .05) will be considered.

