**Figure 1 F1:**
[figure not shown]
Flowchart.

The selected subjects will be divides by block randomization into 3 groups (n per group = 13), according to the treatment to be performed. Opaque envelopes will be identified, and a sheet containing the information of the corresponding experimental group will be inserted. There will be a 1 session for each group (Table 1). All samples from the subjects will be submitted to microbiological analysis and evaluation with Oral ChromaTM before and after treatment, followed by controls of 7, 14, and 30 days.

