### Sample calculation

2.8

For the calculation of the sample size, the data of the work by A. Costa Costa and Mota et al was used. Effect of photodynamic therapy for the treatment of halitosis in adolescents—a controlled, microbiological, clinical trial.^[29]^

Initially we established an error 

, where 

 and 

 are the baseline values for periodontal treatment with PDT. From this error, the effect size, given by

err/√ (σ_1 ^ 2 + σ_2 ^ 2)

where σ_1 ^ 2 and σ_2 ^ 2 are the variances of groups 1 and 2, respectively.

Assuming that the studied groups have a normal or approximately normal distribution, that the sample size will be sufficiently large and that a 2-tailed test will be used, for a significance level α = 0.05 and maintaining the power of the test 1-β = 0.90 we have: In Figure 5 it is observed that with a total sample size of 39 subjects, that is, 3 groups with 13 samples each, the statistical difference should be demonstrated, keeping the power of the test greater than or equal to 0.90. If the normal distribution hypothesis is rejected, the sample size should be corrected by approximately 5%.

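### The stated t test and ANOVA name no baseline covariate although every participant has a pre-treatment reading; with 13 per arm this gives up precision and lets part of any chance imbalance through

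*Protocol article*

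**What the plan says.** Section 2.9 (Organization and statistical processing of data) fixes the between-group method in one sentence: "To compare the means, the Student's *t* test and Analysis of variance (ANOVA) will be used". The sentence then goes straight on to correlation ("Analysis of variance (ANOVA) will be used and to analyze the correlation between the continuous variables"), with nothing on baseline in between. The abstract repeats it. Neither place mentions a covariate, a change score or a repeated-measures form.

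The only method tied to differences is a within-arm one: "In the analyzes of the experimental differences in each group the Wilcoxon test will be used". It compares no treatments.

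Baseline data are nevertheless collected. The text below Figure 1 in section 2.4 plans microbiological analysis and "evaluation with Oral ChromaTM before and after treatment, followed by controls of 7, 14, and 30 days". Participants are "divides by block randomization into 3 groups (n per group = 13" each), and no stratification by baseline level is described. Section 2.8 (Sample calculation) sets "a 2-tailed test will be used, for a significance level α = 0.05 and maintaining the power of the test 1-β = 0.90" and takes no credit for baseline information.

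**The concern.** The baseline reading is the same measurement as the outcome, so it is the natural covariate. Randomization balances it on average, but 39 participants in three arms leave room for sizeable chance differences. A comparison without a baseline term has two costs. It leaves in the error variance the part that baseline could explain, and it lets a fraction of any chance imbalance appear as treatment effect.

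The wording also leaves open whether the compared means are follow-up values or changes. If that is settled after the data are seen, the choice can follow the result.

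**Working it through.** **Inputs.** From the document: 13 per arm, three arms, two-sided α = 0.05, power 0.90. Assumed, because the document does not give them: r = 0.30, 0.45 and 0.60 within arms, with r = 0 as the unfavourable end, and a true difference of 1.0 SD for illustration.

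The r values are a rough allowance for selection on baseline. If entry kept the top 30% of one normal variable (variance ratio 0.264), population correlations of 0.5, 0.7 and 0.8 would shrink to 0.28, 0.45 and 0.57. The 30% is the general prevalence given in the Introduction, and entry is by either of two gases, so this is only a guide.

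**1. The plan's own figure.** Section 2.8 reaches its power "with a total sample size of 39 subjects, that is, 3 groups with 13 samples each". The numbers behind the effect size cannot be read in the available text, so 39 can be neither reproduced nor faulted. Working backwards, a two-arm t test with 13 per arm and 24 degrees of freedom has power 0.90 at a difference of 1.33 SD.

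**2. Chance imbalance.** The standard error of a baseline difference between two arms is √(2/13) = 0.39 SD. A given pair differs by more than 0.4 SD with probability 0.31. At least one of the three pairs differs by more than 0.5 SD with probability 0.41.

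**3. What reaches the outcome.** The unadjusted follow-up difference is shifted by r × imbalance. For 0.4 SD this is 0.30 × 0.4 = 0.12 SD up to 0.60 × 0.4 = 0.24 SD.

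**4. Variance.** Relative to follow-up values alone, ANCOVA has variance 1 − r² and change scores have 2(1 − r). Their ratio is (1 − r²)/(2(1 − r)) = (1 + r)/2, which is below 1 for every r below 1. Change scores are worse than ignoring baseline when 2(1 − r) > 1, that is, r < 0.5.

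**5. Power at 1.0 SD for one pair of arms.** Unadjusted: 0.69 (two-arm t test, 24 df) or 0.70 (error pooled over three arms, 36 df). The ANCOVA figures are simulated, so they include the lost degree of freedom and the cost of estimating the slope. The change-score figures use the noncentral t with 24 df.

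| r | 1 − r² | 2(1 − r) | Two-arm ANCOVA | Pooled three-arm ANCOVA | Change-score t test |
|---|---|---|---|---|---|
| 0 | 1.00 | 2.00 | 0.67 | 0.69 | 0.41 |
| 0.30 | 0.91 | 1.40 | 0.71 | 0.72–0.73 | 0.54 |
| 0.45 | 0.80 | 1.10 | 0.76 | 0.78 | 0.65 |
| 0.60 | 0.64 | 0.80 | 0.85 | 0.86 | 0.78 |

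At r = 0 the loss is 0.69 − 0.67 = 0.02 (two-arm) or 0.70 − 0.69 = 0.01 (pooled).

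**6. Power at 1.33 SD.** Where the unadjusted test already has 0.90, the closed form with 23 df (without the slope cost) gives 0.924 at r = 0.30 and 0.981 at r = 0.60.

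**The case against.** Four points on the other side carry weight.

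- **No error is shown.** Randomization makes the unadjusted test valid. A reader might infer that the planned comparison is biased or invalid, and it is not. The loss is in precision, together with dependence on chance imbalance in the one trial that is run. This stands.
- **The text is silent, not explicit.** A reader might infer that section 2.9 commits to one-way tests on follow-up values that ignore both baseline and the repeated visits. It does not say so: the ANOVA could be a repeated-measures one, and the means could be changes. A condensed article may also leave model details to an analysis plan that is not at hand. This limits the point but does not remove it. The article does name its tests, and adjusting for baseline is better under either reading of the means, unless r is near zero.
- **Imbalance does not pass through whole.** It would be wrong to say that a 0.4 SD baseline difference enters the result in full. Only r times it does.
- **The gain depends on r and on the effect.** If treatment pushes readings towards the floor soon after application, r could be close to zero at that visit, and adjustment would then gain nothing. With a true effect near 1.33 SD there is also little power left to win. Both are fair, and the gain is therefore given as a range.

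**Conclusion.** The point holds as a recommendation to change a stated method, not as an error. Section 2.9 names no baseline adjustment although the reading exists for every participant. At 13 per arm the price is 9% to 36% of the residual variance and a carried-over imbalance of 0.12 to 0.24 SD per 0.4 SD, for an assumed r of 0.30 to 0.60. At 1.0 SD that is a gain of about 0.02 to 0.16 in power with the pooled model. The gain is small at the lower end of r and material from about 0.45.

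The direction is secure. The size rests on a correlation and an effect that the document does not supply. Nothing here shows the sample size of 39 to be wrong.

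**What to change.** In section 2.9, replace the t test and ANOVA wording for between-group comparisons with one of these:

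- at a single visit, one ANCOVA pooled over the three groups, with the post-treatment value as outcome and group and baseline value as terms;
- across visits, a linear mixed model with group, visit, group × visit and baseline as covariate, and participant as random effect.

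Report adjusted group differences with 95% confidence intervals. If values are analysed on a log scale, state how zero readings are handled, since section 2.6 gives a device range that starts at 0 ppb.

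The cost is one paragraph, possibly other software than the package named in section 2.9, and about 0.01 to 0.02 of power if r is near zero. No extra participants, visits or measurements are needed. The change should be made before outcome data are seen.

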**Materials and Methods::**

Young adults in the age group between 18 and 25 years with diagnosis of halitosis will be included in this research. The selected subjects will be divided into 3 groups: G1: aPDT; G2: scraper, and G3: aPDT and scraper. All subjects will be submitted to microbiological analysis and evaluation with Oral ChromaTM before, immediately after treatment, 7, 14, and 30 days after treatment. For the evaluation of the association of the categorical variables the Chi-square test and Fisher's Exact Test will be used. To compare the means the student *t* test and analysis of variance (ANOVA) will be used and to analyse the correlation between the continuous variables the correlation test by Pearson will be applied. In the analyses of the experimental differences in each group the Wilcoxon test will be used. For all analyses a level of significance of 95% (*P* < .05) will be considered.

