### Hypothesis

2.1

Null hypothesis: There is no alteration of halitosis after the use of photodynamic therapy employing the use of blue dye and red LED. There is no microbiological alteration after antimicrobial photodynamic therapy. Experimental hypothesis: there is a decrease in halitosis after the use of photodynamic therapy using blue dye and red LED associated or not with the tongue scraper. There is microbiological alteration after antimicrobial photodynamic therapy.

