### Inclusion criteria

2.3

Young adults between the ages of 18 and 25, with an informed consent form and authorization for the diagnosis and treatment of halitosis. Young adults diagnosed with halitosis presenting Oralchroma S2H ≥ 112 ppb and/or CH3SH ≥ 26.

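### The halitosis hypotheses are before-after statements without a comparator and the changes are tested within each arm, so a significant fall in people enrolled on a high reading does not show an aPDT effect

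*Protocol article*

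**What the plan says.** Section 2.1 gives the null hypothesis as "There is no alteration of halitosis after the use of photodynamic therapy employing the use of blue dye and red LED" and the alternative as "there is a decrease in halitosis after the use of photodynamic therapy using blue dye and red LED", with or without the scraper. Neither names the scraper arm, or any other arm, as the reference.

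Section 2.9 assigns a test to change within arms: "In the analyzes of the experimental differences in each group the Wilcoxon test will be used". It also says that for comparing means the Student's t "test and Analysis of variance (ANOVA) will be used". It does not say which arms, visits or quantities these compare, or which test decides whether aPDT works. The P<.05 criterion applies to every analysis.

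Section 2.3 admits "Young adults diagnosed with halitosis presenting Oralchroma S2H ≥ 112 ppb and/or CH3SH ≥ 26". The same device supplies the breath outcome (section 2.6), measured "before and after treatment, followed by controls of 7, 14, and 30 days". The arms are "G1: aPDT; G2: scraper, and G3: aPDT and scraper", with block randomisation and 13 per arm. No arm is untreated or sham-treated.

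**The concern.** A fluctuating measurement that was selected for being high will on average be lower when repeated, with no treatment at all. A signed-rank test of before against after in one arm counts that drop as effect. The section 2.1 hypothesis asks only whether halitosis is lower after aPDT, so a significant Wilcoxon result in G1 or G3 would satisfy it as worded.

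Randomisation does not protect that inference. It protects comparisons between arms, where the same expected drop occurs on both sides and cancels. The risk is that aPDT is declared effective on a before-after fall even when the arms do not differ, in a trial meant to inform clinicians' choice of treatment.

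**Working it through.** **The plan's own figure.** Section 2.8 gives 39 participants (3 × 13) for 90% power at two-sided α = 0.05. The numerical effect size is not legible in the text at hand, so 39 can be neither reproduced nor refuted. Only the 13 per arm is used below.

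**Inputs from the article:** 13 per arm; two-sided 0.05; enrolment at or above a cut-off on the outcome device; Wilcoxon within arm.

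**Assumptions, shown as ranges because the article does not give them:**
- correlation r between two readings in the same person without treatment: 0.5 to 0.95;
- share of those screened who reach the cut-off: 30%, 50% or 80%. The 30% borrows the population prevalence quoted in the Introduction, which is not the same thing as the share among university students and staff aged 18 to 25;
- normal readings on a log scale;
- the qualifying reading is the baseline.

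**Expected fall with zero treatment effect.** For standardised readings with cut-off c and eligible share q, the mean qualifying reading is φ(c)/q and the mean repeat is r·φ(c)/q. The fall is therefore (1 − r)·φ(c)/q. With q = 0.30, φ(c)/q = 1.159 SD, so the fall is 0.5 × 1.159 = 0.58 SD at r = 0.5, 0.3 × 1.159 = 0.35 SD at r = 0.7, and 0.1 × 1.159 = 0.12 SD at r = 0.9.

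**Chance of a significant fall in one arm when aPDT does nothing.** Simulated with exact two-sided Wilcoxon, single gas, 4,000 trials per cell. A repeat with 20,000 per cell gave the same rounded values; other, smaller runs differed by up to about two percentage points.

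| Share qualifying | r = 0.5 | r = 0.7 | r = 0.8 | r = 0.9 | r = 0.95 |
|---|---|---|---|---|---|
| 30% | 55% | 33% | 23% | 13% | 8% |
| 50% | 28% | 18% | 13% | 8% | 6% |
| 80% | 8% | 7% | 5% | 4% | 4% |

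The reference value without selection is 2.2%; the exact test at n = 13 sits slightly below the nominal 2.5%.

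**Two aPDT arms.** With independent arms, the chance that at least one of G1 and G3 shows a significant fall (30% qualifying) is 1 − (1 − 0.55)² = 80% at r = 0.5 and 1 − (1 − 0.13)² = 24% at r = 0.9. The corresponding reference is 1 − (1 − 0.022)² = 4.4%.

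**Two-gas entry rule.** Section 2.3 admits on either gas. With an assumed correlation of 0.6 between gases and one gas tested, the per-arm chance for r = 0.5 to 0.9 is 39% to 10% (30% qualifying), 21% to 7% (50%) and 7% to 4% (80%).

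**Independent baseline.** If the before reading is a fresh measurement whose error is independent of the qualifying one, the chance returns to about 2.2%.

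**Between-arm test on the same data.** ANOVA on change from baseline is significant in 4.4% to 5.7% of trials across all one-gas and two-gas settings, against a nominal 5%.

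**The case against.** The strongest reply is that this is a randomised three-arm trial whose section 2.9 lists a t test and ANOVA, so a valid between-arm comparison is available and Wilcoxon is not the only test. That is correct. A reader might infer that aPDT will be judged by the Wilcoxon test alone; the article does not say so. What stands is that it does not make the between-arm comparison decisive either, and that section 2.1 asks a question which a between-arm test does not answer. A separate analysis plan may exist, but one faithful to section 2.1 would carry the same problem.

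A second reply is that the size rests on an unstated fact. A reader might infer that the qualifying reading is the baseline. The article describes no separate one, but it does not say they are the same, and the flowchart is not shown. With an independent baseline the regression component largely disappears. The standardised time of day, diet and hygiene also favour reproducible readings, so the right-hand columns of the table may be nearer the truth, and a reading taken immediately after treatment may be less affected than those at days 7 to 30. All of this limits the magnitude. It does not make an uncontrolled before-after test a test of aPDT.

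Three further inferences are not supported:
- The regression argument does not carry over directly to the microbiological hypothesis, because nobody is selected on bacterial counts. A within-arm change in those counts is still uncontrolled.
- The preparation rules do not obviously explain a fall, since section 2.6 applies them to the examination without exempting the first one.
- Nothing in the article plans to infer superiority from one arm being significant and another not, although separate within-arm tests leave room for it.

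**Conclusion.** Wrong as written; should be fixed. The halitosis hypotheses ignore the randomised comparison, and a within-arm Wilcoxon result can satisfy them when aPDT has no effect. That conclusion rests on the text alone.

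The size is conditional, and confidence in it is moderate. It requires the qualifying reading to serve as baseline and depends on two quantities the article does not give. Under those assumptions the false-positive rate for a fall exceeds nominal in every setting tried: severely when few of those screened qualify and readings are only moderately reproducible, and slightly (about 4%) when most qualify and readings are stable. The documents do not support a claim that the design itself is invalid, because the randomised arms allow a sound comparison.

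**What to change.** In sections 2.1 and 2.9:
- Restate the hypotheses as differences between randomised arms, G1 vs G2 and G3 vs G2, in the post-treatment reading or the change from baseline, preferably adjusted for baseline.
- State that the conclusion about aPDT rests only on these contrasts. Word the microbiological hypothesis the same way.
- Keep the within-group Wilcoxon results as descriptive before-after summaries.
- Where a pre-treatment reading separate from the qualifying one exists, use it as the baseline, and say so.

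The cost is wording only; no new data or visits are needed. The downside is that a before-after fall within an aPDT arm can no longer be reported as proof of effect. Because no arm is untreated, a fall shared by all arms could not be credited to treatment. The between-arm contrasts are also demanding at this size: with 13 per arm, a two-sample t test has 90% power only for a difference of about 1.33 SD. That is a reason to adjust for baseline, not to fall back on the within-arm test.

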## Introduction

1

Halitosis is the term used to describe any unpleasant odor related to expired air regardless of its origin.^[1]^ The chemical components related to halitosis are volatile sulfur compounds (VSCs) such as hydrogen sulfide (H2S), methylmercaptanes (CH3SH), and dimethyl sulphide (CH3SCH3).^[2–5]^ The prevalence of halitosis in the population is approximately 30%, of which 80 to 90% of the cases originate in the oral cavity resulting from proteolytic degradation by gram negative anaerobic bacteria from sulfur-containing substrates in saliva, epithelial cells, blood, and food debris.^[6]^

The dorsum of the tongue and periodontal pockets are related as the major niches of bacteria that are responsible for the emission of VSCs. Some methods are used to diagnose halitosis: the organoleptic method, which is a subjective evaluation of the exhaled air of the mouth and nose, and a scale, is used to quantify this odor, depending greatly on the olfactory capacity of the evaluator. Sulphide monitors are devices that quantify the total value of VSC exhaled from the oral cavity. Gas chromatography is the most appropriate method to detect halitosis of different origins because it performs individual measurement of the three main gases (sulfhydride, methylmercaptanes, and dimethyl sulphide), allowing to assess the intensity of the breath and its origin. However, the lack of standardization in the protocol for diagnosis and treatment of halitosis makes it difficult to compare the epidemiological data obtained in different countries.^[7,8]^

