## Discussion

3

Halitosis plays an important role in communication and is related to quality of life and social interaction. Quality of life refers to a person's perception of their position in the system they live in relation to their goals, standard expectations and concerns. It is a comprehensive concept, which is affected by the physical, psychological and social relationship, and relationship with the environment in which it lives. And halitosis is considered one of the problems related to the impact of oral health on quality of life and is enough to affect the individual's perception about his life.^[19]^

Therefore, the need for new treatment alternatives for the patient, especially in the face of the technological advances in dentistry, can work better with the patient's expectation regarding the results.

Because it is a condition that involves mainly anaerobic bacteria, which release the SVC in the exhaled air and are responsible for the bad smell. Its main cause is related to the presence of these microorganisms in the lingual flap. And so, it must work to reduce the number of microorganisms responsible for this problem.

There is still a great deal of divergence in the literature regarding the epidemiological data of this condition due to the lack of standardization in the diagnosis, and the treatment proposed in the literature is broad that consists of the chemical and mechanical reduction of the tongue coating.^[9–13]^

In the initial studies in this area it was possible to observe an immediate result, with the elimination of bad odor by the reduction of CSV concentration specifically of the levels of SH2 when the treatment with photodynamic therapy was used in the dorsum of adolescents with halitosis.^[29–33]^

The present study proposes to conduct a controlled clinical trial to evaluate the effectiveness of the application of aPDT in the tongue coating as a new proposal for treatment and control of halitosis, mainly because it is a fast, non-invasive procedure and does not generate bacterial resistance, as evidenced in the studies cited below and published.

Not generating bacterial resistance can be considered one of the great advantages of aPDT, due to the great problem that we are currently with the development of superbugs being these resistant to the broader antibiotics.

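### P<.05 is fixed for every analysis and no primary outcome, time or contrast is named, so the false-positive risk is several times 5% and the stated power belongs to no identified test

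*Protocol article*

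**What the plan says.** Section 2.9 names the chi-square and Fisher tests for categorical variables, Student's t test and ANOVA for means, Pearson correlation, and the Wilcoxon test for differences within each group. It closes with "For all analyzes a level of significance of 95"% (P < .05). The figure of 95% is evidently a slip for 5%. The abstract repeats the rule.

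The tests would be applied to the following:
- **Arms:** "block randomization into 3 groups (n per group = 13"), so there are three arm pairs.
- **Times:** measurements "before and after treatment, followed by controls of 7, 14, and 30 days" (section 2.4, randomisation paragraph). The abstract makes clear that the first post-treatment reading is immediate, which gives four post-treatment times.
- **Gases:** the Introduction says of gas chromatography that "it performs individual measurement of the three main gases", and section 2.6 gives a reference level for each of the three.
- **Bacteria:** section 2.5 names three species for quantitative PCR.

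Section 2.1 sets two null hypotheses of equal rank, one on halitosis and one on microbiology. Neither names a gas, species, time or contrast. Section 2.8 sizes the trial "for a significance level α = 0.05 and maintaining the power of the test 1-β = 0.90", assuming "that a 2-tailed test will be used". Its readable text does not say which gas, time or contrast that power serves.

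**The concern.** A rule of .05 for everything controls error only test by test. The hypothesis in section 2.1 is worded broadly enough that a fall in any gas, at any visit, in either aPDT arm could be read as confirming it. The result that becomes the headline can then be picked after the data are seen. The power statement has the same weakness: 90% at 0.05 means something only for one identified comparison. The article says the results could support clinicians' decisions on aPDT, so a chance finding in one cell could be taken up as evidence of efficacy.

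**Working it through.** **1. The plan's own figure.** Section 2.8 gives 39 subjects (3 x 13) for power of at least 0.90 at two-sided 0.05. Its effect size is "err/√ (σ_1 ^ 2 + σ_2 ^ 2"), but the error term and variances are not legible in the text available, so 39 can be neither reproduced nor refuted. Working backwards, a two-sample t test with 13 per arm (24 df, critical value 2.064) reaches 90% power at a standardised difference d of about 1.326. That holds for one pair and one test at unadjusted 0.05.

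**2. Counting tests.** Three gases x 4 times x 3 pairs = 36 between-arm tests. With the three named species, 6 x 4 x 3 = 72. Within-arm Wilcoxon tests against baseline number 3 gases x 4 times x 3 arms = 36, or 72 with the species.

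**3. Independence formula, for orientation only.** 1 - 0.95^3 = 14.3%, 1 - 0.95^12 = 46.0%, 1 - 0.95^36 = 84.2%. These overstate the pairwise case, because three pairs among three arms share data. By simulation, one gas at one time with three pairwise t tests gives about 12%, not 14.3%. All 36 tests give about 80%, not 84%, even with gases and times independent.

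**4. Simulation under a global null.** Setup: 13 per arm, normal data, equal correlation between all times and between all outcomes, t tests at two-sided .05. The correlations are assumptions, since the article gives none. The gated column counts a pair only where the ANOVA for that gas and time is significant (F on 2 and 36 df). Repeat runs differ by one or two points.

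| Correlation (time, outcome) | 3 gases, pairwise t | 3 gases, ANOVA first | 3 gases + 3 species, pairwise t |
|---|---|---|---|
| 0.3, 0.3 | 76% | 42% | 92% |
| 0.5, 0.5 | 67% | 36% | 85% |
| 0.7, 0.5 | 60% | 32% | 79% |
| 0.8, 0.7 | 48% | 24% | 65% |

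The smallest entry, 24%, is 24/5 = 4.8 times the nominal level.

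**5. Adding the within-arm tests.** If any significant Wilcoxon test against baseline also counts, the ANOVA-first total for three gases is about 64-85%, over correlations of 0.3-0.9 between gases and 0.5-0.9 between times.

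**6. Cost of sharing alpha.** The noncentrality at d = 1.326 is 1.326 x sqrt(13/2) = 3.38. At alpha 0.05 (critical t 2.064) power is 90%. At 0.025 (critical t 2.391) it is about 83%. At 0.05/3 (critical t 2.574) it is about 78%.

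**The case against.** Several objections have force.

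- **ANOVA is listed beside the t test.** A reader might infer that the plan prescribes three unadjusted t tests per outcome. Section 2.9 does not say so: it names both methods and does not say which applies where. It states no gate either, so both readings must be shown. The ANOVA-first reading roughly halves the figures.
- **The correlations are assumed.** At 0.9/0.9 the pairwise figure for three gases falls to about 34%.
- **The third gas may not be an efficacy outcome.** Section 2.3 defines halitosis by hydrogen sulphide and/or methylmercaptan, and section 2.6 attributes dimethyl sulphide to periodontal, systemic or dietary causes. With two gases the pairwise figures are about 62%, 54%, 48% and 40% at the same four settings. That is lower, but still at least 8 times 5%.
- **A global null may be too pessimistic.** The Discussion reports that "In the initial studies in this area it was possible to observe an immediate result". Earlier evidence for an immediate effect does not protect claims about later visits, other gases or bacteria.
- **A multiplicity procedure may sit in an analysis plan that is not shown.** This is a fair reason not to fault missing detail. But the article states one threshold for all analyses, which a later procedure would contradict, and the sample size calculation needs an identified primary comparison.

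The objections reduce the size of the problem and do not remove it.

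**Conclusion.** The defect holds: one threshold is fixed for everything, and no outcome, species, time or contrast is named as primary. For three gases at four times, the family-wise error is about 48-76% with unadjusted pairwise t tests and about 24-42% if pairs follow a significant ANOVA. Bacterial targets and within-arm tests raise both. These figures assume no true effect anywhere, 13 per arm, normal data and the stated correlations.

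Two stronger readings are not supported. One is that a false-positive finding is more likely than not: the between-arm figures fall below 50% at the high-correlation end and throughout the ANOVA-first column for gases. The other is that the error is 84%: that value needs independent arm pairs, which this design cannot have. Nor do the documents single out a particular visit or contrast as the right primary one, since section 2.1 covers aPDT with or without the scraper.

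**What to change.** Before any outcome data are examined, name one primary outcome, one time and one between-arm contrast, and test it two-sided at 0.05. An example is hydrogen sulphide at one stated follow-up visit, aPDT plus scraper v scraper; the investigators may prefer another. Then test the other times in a fixed order at 0.05, stopping at the first non-significant result. This needs no split of alpha.

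If both aPDT arms v scraper are to be co-primary, apply Holm over the two contrasts at the primary time (smaller P against 0.025, then the larger against 0.05) and treat later times as secondary. Restate the power at the first-step alpha of 0.025. At the difference that gives 90% at 0.05, it is about 83%.

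Replace the closing rule of section 2.9 accordingly, state which test is used for the primary contrast, and tie section 2.8 to it. Report the other gases, any times outside the testing order, bacteria, within-arm changes and correlations as exploratory, with confidence intervals.

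The cost is a few sentences. Fewer results can be called significant, and power falls somewhat only if two contrasts share alpha.
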